## Methods

### Trial Design

We will conduct a prospective, 2-group crossover RCT with a 1:1 allocation ratio to either the intervention (VR-PAT gameplay) or the control (VR headset turned off) for the first laser appointment. Participants will crossover to the opposite group at their second laser appointment. Pain, anxiety, and VR engagement (for those in the intervention group) will be assessed after each research appointment, spaced approximately 6 to 8 weeks apart. The findings will be reported based on the CONSORT (Consolidated Standards of Reporting Trials) guidelines. This protocol is reported in accordance with the SPIRIT (Standard Protocol Items: Recommendations for Interventional Trials) guidelines (Checklist 1).

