#### Observed Measures (Research Collected)

The Modified Yale Preoperative Anxiety Scale (mYPAS) [37] will be assessed at each laser procedure before entering the treatment room, before the procedure begins, and immediately following the procedure. This is a 5-item scale, with a score of more than 30 indicating anxiety. During the procedure, the researcher will document the start and stop times of the laser procedure, the start and stop times of the VR (if applicable), whether the participant declined to use the VR-PAT, and the number of voluntary interruptions of the VR-PAT.

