#### Primary Outcomes

Difference in self-reported worst pain, average pain, and time spent thinking about pain (NRS 0 [min]−10 [max]) between VR-PAT and control visits. These questions are asked at each visit and will be compared between the intervention and control visits.

Change in procedural anxiety (mYPAS observed by the researcher, 23.33 [min]−100 [max], with higher scores denoting higher levels of anxiety) is assessed at 3 time points: prior to entering the procedure room, prior to the procedure, and immediately following the procedure for each laser procedure. These differences will be compared before and after the procedure, as well as between the intervention and control visits.

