### Sample Size

Since this is a pilot study, the focus of the statistical analysis will be on estimating the effect sizes of VR-PAT and their 95% CI, as well as the variances of the outcome measures. These findings will facilitate sample size calculations and study power estimates for future larger-scale randomized trials. We decided on a sample of 40 participants and 2 research visits based on the grant budget and the patient volume for the 1 dermatologist collaborating on this study.

Across acute pain studies, clinically meaningful improvements are generally larger than a 1-point change on the NRS 0‐10, with systematic review evidence suggesting minimum clinically important differences of approximately 13% to 36% reduction, with a median of 23% (IQR 18%-36%), corresponding to roughly 1.4‐2.3 points on the NRS [38,39].

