For aim 2, the mYPAS score had 6 repeated measurements over time (T0, T1, and T2 during each of the 2 laser procedures). At the first procedure, we will compare the change in mYPAS scores from T0 to T1 and T0 to T2 between the control and VR groups using either 2-sample 1-tailed *t* tests or the Wilcoxon rank sum tests (depending on the distribution of the change in mYPAS scores). The clinical effect size will be the difference in medians of the change in mYPAS, with the confidence limits calculated by bootstrapping with replacement using 1000 repetitions. Bootstrapping has been found to provide better confidence limits with asymmetric data, such as the mYPAS score in our study, and is the recommended method. The same statistical analysis approach has been successfully used by other researchers, who reported that VR effectively reduced preoperative anxiety among 71 children aged 5 to 12 years scheduled for elective surgery [42]. At the second procedure, we will compare the mYPAS scores at T0 and T1 between the control and VR groups using the Wilcoxon rank sum tests since mYPAS scores are shown to be asymmetric [42]. The clinical effect size will be the difference in medians of mYPAS. Confidence limits will be calculated using bootstrapping again.

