## Results

This study was funded by an intramural grant from the Clinical and Translational Science Institute at NCH (grant: IFPAWRI012023) in January 2023. Enrollment started in January 2023, and data collection was completed in November 2025. The flow of participants can be seen in Figure 1. A total of 44 patients were recruited and completed the first visit, with 40 participants completing both visits. The sample was balanced, with 40 patients using the VR intervention and 40 patients participating in the control group. Reasons for not completing both visits included discontinuing laser treatment (n=3) and a lack of interest in playing the VR game (n=1). Among those who completed both visits, the age range of the sample was 6 to 21 years at recruitment, and 55% (n=22) were female. Data analysis is expected to be finished in June 2026, with a paper to follow. Future results will be disseminated through publications in peer-reviewed journals and abstracts submitted to conferences in relevant disciplines.

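### The visit-1 mYPAS comparison uses unadjusted change from T0, although T0 is collected and could be adjusted for; the test is valid but gives up some precision

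*Protocol article*

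**What the plan says.** The Primary Outcomes section lists "Change in procedural anxiety (mYPAS observed by the researcher, 23.33 [min]−100 [max], with higher scores denoting higher levels of anxiety") beside three self-reported pain items. Under Observed Measures, the scale "will be assessed at each laser procedure before entering the treatment room, before the procedure begins, and immediately following the procedure"; Data Analysis calls these times T0, T1 and T2.

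For the first procedure the plan is explicit: "we will compare the change in mYPAS scores from T0 to T1 and T0 to T2 between the control and VR groups". The test is a t test or a Wilcoxon rank sum test, chosen by how the change is distributed, and the wording "using either 2-sample 1-tailed" shows that it is one-sided. The effect measure is the difference in median change, with bootstrap limits from 1000 repetitions. The section justifies the approach by the asymmetry of mYPAS and by an earlier study of 71 children that analysed the scale in the same way.

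Covariates appear only in the linear mixed models, and those are fitted to the pain composite. There mYPAS (the average of T0 and T1) is a predictor and never the outcome. On purpose, the Sample Size section says "the focus of the statistical analysis will be on estimating the effect sizes of VR-PAT and their 95% CI", together with variances for planning larger trials.

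**The concern.** Subtracting T0 is a form of adjustment that fixes the slope of the later score on T0 at 1. If the true slope is lower, as it is when rho is below 1 and the variances are equal, subtraction over-corrects and adds T0 noise to the comparison. With about 20 to 22 participants per group and no stratification, chance differences in T0 can be appreciable. A participant who starts near the scale minimum of 23.33 also has little room to fall.

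What is at stake is the precision of one primary-outcome estimate in a pilot whose stated purpose is estimation. The variance carried forward matters too: the variance of an unadjusted change score would oversize a later trial that is analysed with T0 adjustment.

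**Working it through.** **Inputs from the protocol.** The planned sample is 40 ("We decided on a sample of 40 participants and 2 research visits based on the grant budget") in a "2-group crossover RCT with a 1:1 allocation ratio", so 40/2 = 20 per group. The Results section reports "A total of 44 patients were recruited and completed the first visit", so 44/2 = about 22 per group at visit 1. The tests are one-tailed.

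**Inputs assumed.** The protocol gives no alpha, power, SD, effect or rho for mYPAS, so there is no stated figure to reproduce. I take a one-tailed 5% level, SD = 1 at both times, an effect of 0.5 SD and rho from 0.3 to 0.9.

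**Formulas (difference in means).**
- Variance per participant, change score: 2(1 − rho).
- Variance per participant, adjusted for T0: 1 − rho².
- Ratio: (1 − rho²) / [2(1 − rho)] = (1 + rho)/2, which is below 1 for every rho below 1.
- Reduction in standard error: 1 − √[(1 + rho)/2].
- Power: noncentral t with noncentrality 0.5 / √(2 × variance / 22), on 42 df for change and 41 df for the adjusted analysis.

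Worked line at rho 0.5: the variances are 1.00 and 0.75, the ratio is 0.75, and the noncentralities are 0.5/√(2 × 1.00/22) = 1.66 and 0.5/√(2 × 0.75/22) = 1.91.

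| rho | variance ratio | SE reduction (mean) | power, change | power, adjusted | gain (points) |
|---|---|---|---|---|---|
| 0.3 | 0.65 | 19.4% | 39.5% | 52.6% | 13.1 |
| 0.5 | 0.75 | 13.4% | 49.5% | 59.4% | 9.9 |
| 0.7 | 0.85 | 7.8% | 67.8% | 73.8% | 6.1 |
| 0.8 | 0.90 | 5.1% | 82.5% | 85.8% | 3.3 |
| 0.9 | 0.95 | 2.5% | 97.7% | 98.2% | 0.5 |

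Gains are computed before rounding. With 20 per group they are close: 12.3, 9.5, 6.1, 3.6 and 0.6 points. Across rho 0.2 to 0.9 and effects of 0.5 to 1.0 SD, with 20 per group, the gain runs from about 0 to 19 points.

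**Skewed, bounded scores.** These were simulated with 4000 runs per setting, 20 per group, an assumed log-normal shape clipped to 23.33–100, and a shift of 0.6 SD on the latent scale. Power of the rank sum test on change against rank ANCOVA on T0 was 35% v 59% (rho 0.3), 43% v 65% (0.5), 58% v 78% (0.7) and 80% v 93% (0.85). Part of that gain comes from ranking the scores themselves. On the raw scale at rho 0.5, the t test on change had 39% and ordinary ANCOVA 56%. Type I error was about 5% for all four methods.

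**The planned effect measure.** The formula above is for means, whereas the plan bootstraps a difference in medians. In simulations with 22 per group, the standard error of T0-adjusted median regression was compared with that of the difference in median change. Results varied between simulations. For normal scores the reduction was 12–15% at rho 0.5, 2–8% at 0.7, 1–5% at 0.8 and none at 0.9, reaching about 20% at rho 0.3. For skewed, floored scores it was 7–8% at rho 0.5, 1–4% at 0.7, 6–9% at 0.8 and none at 0.9, reaching about 15% at rho 0.3. The overall range is roughly 0 to 20%, generally lower under skew.

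**The case against.** The strongest reply is that nothing here is an error. Under randomisation a two-sample comparison of change is valid, and its type I error is near 5% in the simulations. A reader might infer from the dependence on chance T0 imbalance that the estimate is biased. It is not: that dependence is sampling variation, which the interval already reflects. The method was stated openly and follows a published precedent on the same scale. This stands, and it limits the point to lost efficiency.

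A reader might also infer a fixed cost of about 10 points of power. The protocol does not support that, because the figure needs rho near 0.5. All measurements at a visit fall close together, so a higher rho and a smaller loss are plausible, though the document cannot settle it. Power was also not the basis for the sample size, so the effect on the interval matters more, and for medians that effect is modest and can be nil.

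Nor is this the pilot's key interval. Data Analysis attaches the label of primary analysis to the pain composite, and mYPAS change is one of several primary outcomes.

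Finally, adjustment has its own costs. Rank ANCOVA and median regression target different quantities, so test and estimate need not agree exactly. Under skew and a floor, the adjusted median difference is not the same summary as the difference in median change. Data collection has ended and analysis is under way. These are reasons to keep the planned summary and document the change, and they do not remove the gain.

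**Conclusion.** The point holds as one of precision. The protocol fixes an unadjusted change-score comparison for a primary outcome in groups of about 20 to 22, with T0 in hand and unused except by subtraction. This is a choice written into the article, so it is not a detail left to an unseen analysis plan.

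Under the assumptions shown (22 per group, 0.5 SD, one-tailed 5%, equal variances), the power given up falls from about 13 points at rho 0.3 to under 1 at rho 0.9. The standard error of a median-based estimate would fall by roughly 0 to 20%. The change is worth making because the pilot is meant to deliver effect sizes, intervals and variances, and because it costs little.

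One premise is open. Randomization and Blinding places randomisation after the baseline survey, and Participant Timeline says anxiety levels are collected before randomisation. Neither says whether the visit-1 T0 mYPAS was scored before assignment was known. If it was not, T0 is not a clean baseline for either the change score or the adjusted analysis.

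**What to change.** In Data Analysis (aim 2, first procedure), before the biostatistician is unblinded:

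- Specify a comparison of mYPAS at T1, and separately at T2, on randomised group with adjustment for the visit-1 T0 score. Use rank ANCOVA for the test, and median regression with the planned 1000-repetition bootstrap for the effect and its 95% CI.
- Report the planned unadjusted difference in median change alongside, since the summaries differ under skew and this one matches the cited 71-child study.
- Date and document the change. If that cannot be done before unblinding, keep the planned analysis and report the adjusted one as a labelled sensitivity analysis.
- State whether visit-1 T0 was scored before assignment was known.

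The cost is one degree of freedom and a documented change to the analysis. No new data are needed.

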### Randomization and Blinding

A block randomization scheme with a block size of 4 will allocate participants to 1 of the 2 intervention sequences (VR-PAT followed by control or control followed by VR-PAT) at a 1:1 ratio without stratification. We chose a block randomization strategy to avoid imbalances in allocation to the intervention at the first visit in case we were unable to recruit our planned sample. The randomization scheme was developed and uploaded to a study-specific REDCap (Research Electronic Data Capture; Vanderbilt University) project by the project manager. Study participants are randomized into intervention sequences after signing consent and completing the baseline survey. Research recruiters and participants are not aware of the intervention assignment until the participant is randomized in REDCap.

We cannot blind the participants or the clinical team to the assigned intervention since the headset will either be turned on or off. The researcher who randomized the participant and observed the laser procedure will not be blinded, but a second researcher, who is blinded to the intervention group, will collect pain ratings and anxiety post procedure. The second researcher will wait in a different room during randomization and the laser procedure, and the first researcher will remind the participant at the end of the laser procedure to keep their group a secret until they are asked. The study biostatistician will also be blinded to the intervention group while performing analyses on the primary outcome. The data will be blinded by removing labels such as “VR” and “Control” and replacing them with unidentifiable letters (eg, “A” and “B”). The biostatistician will need to be unblinded for secondary outcomes, as only participants in the intervention group will answer the VR experience questions.

The blinded researcher will need to be unblinded after pain and anxiety ratings are obtained, as those in the control environment will not be able to answer the VR experience questions. The researcher will become unblinded by asking participants whether they played the game. The biostatistician will also be unblinded for full analyses by being provided with the full dataset, including complete data labels and VR questions. This unblinding will take place after the primary outcome analysis has been completed.

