## Discussion

Our VR-PAT protocols have been successfully implemented in our prior and ongoing studies, and we believe this protocol will be successful in a new setting. Prior VR research has been shown to significantly reduce self-reported pain [21-23], anxiety [10,24], and time spent thinking about pain [10,23] during painful pediatric procedures. Similar findings are anticipated in this outpatient laser study. The authors also anticipate very few reports of simulator sickness, as this study uses the same VR-PAT that has been previously used during pediatric burn dressing changes [29,31], in the emergency department [43], and during pin-pulling procedures [43]. We expect this intervention to be feasible to implement, with nurses reporting a high degree of helpfulness and ease of use, similar to our previous work [29].

The strength of this study is that laser procedures are unique clinically, in that the pain stimulus is the same for each procedure. This allows the use of a crossover study design and within-participant comparisons. Our prior VR research has been conducted during burn dressing changes, which are subject to healing over time, making each dressing change a different pain experience. Another strength of this study is providing pain and anxiety distraction during an outpatient procedure, which has historically been difficult to achieve. To maintain laser safety, shiny surfaces must be limited to avoid a reflection of the laser beam, and ocular safety requires glasses that filter the light waves and can alter the colors that patients can see. Since our VR headset passed laser safety testing, it can be a valuable tool for this patient population. Finally, we have found that the proportion of participants recruited is high among those we have approached and retention has been high among those patients who returned to the clinic for their second laser visit. Part of the retention success can be attributed to the study’s buy-in from the clinic nurses. They have helped to keep excitement high among participants by talking to them about the VR game during the laser procedures, and they have even developed an anonymized scoreboard for participants to keep track of their scores. The nurses also keep the VR headset charged and clean to ensure the study implementation runs smoothly.

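### mYPAS change is a primary outcome contrasted between VR and control visits, but it is analysed only by unpaired tests one visit at a time, with a different endpoint at each visit

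*Protocol article*

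**What the plan says.** Under Primary Outcomes the article lists "Change in procedural anxiety (mYPAS observed by the researcher", on three occasions per procedure, and adds: "These differences will be compared before and after the procedure, as well as between the intervention and control visits". Every participant is meant to have one visit of each kind. The Discussion gives the stable pain stimulus as the reason for the design: "This allows the use of a crossover study design and within-participant comparisons".

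The Data Analysis section handles anxiety (aim 2) as follows:

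- **First procedure:** "we will compare the change in mYPAS scores from T0 to T1 and T0 to T2 between the control and VR groups", by a 2-sample 1-tailed t test or a Wilcoxon rank sum test.
- **Second procedure:** rank sum tests of the mYPAS score itself at T0 and T1. Change is not analysed and T2 does not appear.
- **Effect size at both:** a difference in medians between groups, with bootstrap limits.

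The Abstract describes rank sum tests of mYPAS change at each visit.

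For pain (aim 1), the same section uses paired t or signed rank tests, citing the crossover, and promises the SD of the difference. The mixed models with participant intercepts are fitted to the pain composite; mYPAS enters them only as a covariate.

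**The concern.** The outcome definition, read naturally in a crossover, asks how a participant's anxiety change under VR differs from the same participant's change under control. The analysis compares different people within one visit. Nothing specified for mYPAS uses the fact that both conditions were observed in the same 40 participants, and no reason is given for treating anxiety differently from pain.

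The change of endpoint makes this worse. If both visits used the same change score, averaging the two between-group differences would recover a period-adjusted crossover estimate. They do not, so the T0–T2 effect rests on visit 1 alone and the visit-2 T2 measurements have no planned use in the aim 2 tests.

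What is at stake is what the pilot says it is for: effect sizes, their 95% CIs and outcome variances for planning a larger trial. For anxiety, the CI will be wider than the data allow, and no SD of the within-participant difference will be available to size a later crossover on mYPAS.

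**Working it through.** **The three descriptions side by side**

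| Place | Visit 1 | Visit 2 | Comparison |
|---|---|---|---|
| Primary Outcomes | change | change | before v after; VR visit v control visit |
| Abstract | change | change | between groups, at each visit |
| Data Analysis | change T0–T1, T0–T2 | score at T0, T1; no T2 | between groups, at each visit |

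By the order of assessments under Observed Measures, T0 and T1 both precede the procedure and T2 follows it. Visit 2 as planned therefore has no post-procedure anxiety comparison.

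**Inputs from the documents**

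- Allocation: "A block randomization scheme with a block size of 4 will allocate participants to 1 of the 2 intervention sequences", 1:1.
- Numbers: "A total of 44 patients were recruited and completed the first visit, with 40 participants completing both visits". Forty-four is 11 complete blocks of 4, so about 22 v 22 at visit 1. Forty at visit 2 is about 20 v 20; the exact split depends on which sequences lost the four.
- The article makes no power calculation: "We decided on a sample of 40 participants and 2 research visits based on the grant budget and the patient volume". There is no stated figure to reproduce.

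**Assumptions (not in the documents)**

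- SD of mYPAS change = 1, so results are in SD units.
- Correlation ρ of change scores between the two visits: 0, 0.3, 0.5, 0.7.
- One-sided α = 0.05 for power, matching the 1-tailed t test; illustrative effect 0.5 SD.
- Normal theory on means. The planned effect size is a difference in medians, so absolute values would differ in practice.

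**Standard errors**

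- Between groups, one visit: SE = √(2/n). For n = 22, √(2/22) = 0.302. For n = 20, √(2/20) = 0.316.
- Within participant, 40 completers, period-adjusted: SE = √(2(1−ρ)/40).

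| ρ | SE within | 22 v 22 SE ÷ within | 20 v 20 SE ÷ within | 95% CI half-width | Detectable at 80% power | Power at 0.5 SD |
|---|---|---|---|---|---|---|
| 0 | 0.224 | 1.35 | 1.41 | 0.45 | 0.57 | 71% |
| 0.3 | 0.187 | 1.61 | 1.69 | 0.38 | 0.47 | 84% |
| 0.5 | 0.158 | 1.91 | 2.00 | 0.32 | 0.40 | 93% |
| 0.7 | 0.122 | 2.46 | 2.58 | 0.25 | 0.31 | 99% |

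The same quantities for one visit as planned:

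| Groups | 95% CI half-width | Detectable at 80% power | Power at 0.5 SD |
|---|---|---|---|
| 22 v 22 | 0.61 | 0.76 | 50% |
| 20 v 20 | 0.64 | 0.80 | 46% |

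(CI half-widths and detectable differences in SD; power from the noncentral t, with 38 df for the within-participant analysis.)

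**Variance ratio.** For 22 v 22 it is (2/22) ÷ (2(1−ρ)/40) = 1.82/(1−ρ), that is 1.8, 2.6, 3.6 and 6.1. For 20 v 20 it is 2/(1−ρ), that is 2.0, 2.9, 4.0 and 6.7. The visit-1 analysis would match the within-participant one only if 1−ρ = 1.82, a correlation of −0.82. The direction therefore does not hinge on the assumed range; the size does.

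**The case against.** The best defence is carryover. The Introduction says that darkness from eye protection and procedural distress can provoke phobic reactions that affect later treatments, and the control condition is a dark screen. Anxiety at visit 2 could well depend on which condition came first. A randomised visit-1 comparison avoids this; a within-participant estimate does not. That stands, and it is why the visit-1 test should be kept. It does not justify the plan as written. The article does not give carryover as its reason, its first-procedure-only fallback concerns the pain composite and applies only if carryover is detected, and the planned visit-2 comparison is itself exposed to carryover.

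The pilot status also counts. The article claims no power, and none of its scale-up thresholds depends on mYPAS, so the power figures contradict nothing stated. But estimation is the declared focus, and precision is what is lost.

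A reader might infer more than the documents support:

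- *That the VR effect on anxiety is never estimated, or is biased.* Visit 1 does give a valid estimate of the VR effect on mYPAS change.
- *That aim 2 yields two rival answers needing a rule to combine them.* The visits measure different things: change at visit 1, and pre-procedure scores after a different first experience at visit 2. The problem is the unexplained switch of endpoint.
- *That the loss of information is a known, large figure.* The correlation of change scores across visits about 6 to 8 weeks apart is not given, and at zero correlation the visit-1 SE is only about 1.3 times the within-participant one.

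**Conclusion.** The point holds as a loss of precision and an inconsistency between sections. The between-visit contrast in Primary Outcomes has no matching within-participant analysis, and Data Analysis contradicts the Abstract on what is compared at visit 2. Relying on visit 1 alone gives an SE about 1.3 to 2.5 times that of the within-participant analysis (1.4 to 2.6 times for 20 v 20), for assumed correlations of 0 to 0.7. One-sided power at 0.5 SD is about 46–50% against 71–99%, as illustration only. These figures also assume equal variances at both visits and negligible carryover. The validity of the visit-1 comparison is not in question.

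**What to change.** Before the biostatistician is unblinded, and with a dated justification:

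1. Make the aim 2 analysis the period-adjusted within-participant VR-minus-control difference in mYPAS change over both visits, for both T0–T1 and T0–T2.
2. Because the article expects mYPAS to be asymmetric, a rank-based comparison of period differences between the two sequences is suitable, with a Hodges–Lehmann CI or a bootstrap that resamples participants. A mixed model with participant intercept, treatment and period is an alternative.
3. Report the SD of the within-participant difference, as is already planned for pain.
4. Keep the visit-1 between-group comparison as the carryover-free sensitivity analysis.
5. Reconcile the Abstract, Primary Outcomes and Data Analysis on endpoint, time points and comparison. If the visit-2 T0 and T1 score comparison is kept, say what separate question it answers.

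No new data are needed. The costs are a documented change to a primary analysis after data collection has ended, which is credible only if made while treatment labels are still masked, and an estimate that relies on limited carryover. Showing the visit-1 result beside it lets readers judge that reliance.

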**Conclusions:**

Findings from this innovative randomized clinical trial will provide early evidence on the efficacy of the VR-PAT in reducing self-reported pain and anxiety during outpatient laser procedures. The results from this trial will inform a large-scale, multisite study.

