### Data Analysis

To achieve aim 1, composite scores will be calculated for each laser procedure, encompassing the pain score, pain medication use during the procedure, and whether rescue medication was used. The rationale for choosing the composite score as the outcome is that prior researchers have shown a significantly high positive relationship between pain medication use and self-reported pain scores [40]. From a clinical perspective, pain scores alone are influenced by the patients’ actual opioid use and may not fully reflect the treatment benefit of VR [41]. The composite score approach, therefore, provides a single, patient-centered outcome that represents overall analgesic benefit, aligning with the goal of achieving adequate pain control while minimizing opioid exposure. In our analysis, we will apply the rank-based approach by Dai et al [40] to assign weights to pain and medication use, reflecting their complementary clinical importance as measures of pain reduction [41]. In the primary analysis, the composite scores from the laser procedure with VR will be compared to those from the procedure with standard care (ie, control) using paired 1-tailed *t* tests or the Wilcoxon signed rank tests (depending on the distribution of the composite scores) due to the cross-over design. The clinical effect size will be the mean difference (if paired *t* tests are used) or median difference (if Wilcoxon signed rank tests are used) in the composite score between VR and control procedures. The SD of the difference will also be calculated.

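### Aim 2 rests on four unranked mYPAS comparisons on two scales, only one of which includes a rating taken after VR use at that visit

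*Protocol article*

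**What the plan says.** Primary Outcomes lists change in observer-rated procedural anxiety (mYPAS) as a primary outcome. It "is assessed at 3 time points: prior to entering the procedure room, prior to the procedure, and immediately following the procedure for each laser procedure". The same paragraph says the differences will be compared before against after the procedure, and between intervention and control visits. The Methods part of the abstract says the change in mYPAS will be compared between VR and control at each visit.

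Data Analysis carries this out differently. For the first procedure it will "compare the change in mYPAS scores from T0 to T1 and T0 to T2 between the control and VR groups". The tests for these two changes are t tests, described as "using either 2-sample 1-tailed", or else rank sum tests. The plan for the other visit reads: "At the second procedure, we will compare the mYPAS scores at T0 and T1 between the control and VR groups". No sidedness is given there; the method is stated as "using the Wilcoxon rank sum tests since mYPAS scores are shown to be asymmetric". The effect size is the difference in medians of the change at visit 1 and the difference in medians of the raw score at visit 2, each with bootstrap confidence limits. No contrast is named as the main one for aim 2, and the two visits are not combined.

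Pain has its own test: "In the primary analysis, the composite scores from the laser procedure with VR will be compared" with those from the control procedure. Sample Size describes a pilot focused on effect sizes, 95% CIs and variances, to be used in sizing later trials. The abstract concludes that the findings "will provide early evidence on the efficacy of the VR-PAT in reducing self-reported pain and anxiety during outpatient laser procedures".

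**The concern.** An outcome listed as primary should have one quantity that answers its aim. Here there are four, on two scales, and they do not measure the same thing. Some are taken before VR can have acted at that visit, yet all four are presented alike as comparisons of VR with control.

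Two consequences follow. First, the article intends its effect sizes to feed the next trial's sample size. With four anxiety estimates and none designated, that input can be chosen after the results are seen. Second, the article attaches tests to these contrasts and speaks of early evidence of efficacy for anxiety. A reader could then take one favourable p-value out of four as that evidence, although it may come from a rating made before the game was played at that visit.

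**Working it through.** **1. What each contrast can show.** I take T0, T1 and T2 to be the three ratings in the order listed: before entering the treatment room, before the procedure begins, and immediately after it (Observed Measures; Primary Outcomes). Participant Timeline says VR is played during the procedure.

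| Contrast in Data Analysis | Scale | Rating after VR use at that visit? |
|---|---|---|
| Visit 1, T0 to T1 | change | No |
| Visit 1, T0 to T2 | change | Yes |
| Visit 2, T0 | raw | No; rated before entering the room |
| Visit 2, T1 | raw | No |

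T2 is rated at both visits, but no planned comparison uses it at visit 2.

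**2. Fit with the article's other statements.** The abstract's change at each visit is met at visit 1 only. The comparison between intervention and control visits in Primary Outcomes is within participant; all four mYPAS tests compare separate groups within a visit.

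**3. Effect of a stable difference between sequences.** Let d be the chance difference in habitual anxiety, VR-first minus control-first.
- Visit-1 change, VR minus control: d enters both T0 and the later rating, so d − d = 0.
- Visit-2 raw score: the VR group is now the control-first sequence, so the contrast is shifted by −d.

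With 40 participants allocated 1:1 (20 per sequence) and a between-participant SD of σ in habitual level, the standard error of d is σ√(1/20 + 1/20) = 0.316σ. Only the visit-2 raw contrasts carry this. It is ordinary sampling error, which the test allows for, but it makes those estimates noisier and hard to set beside the visit-1 changes.

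**4. Chance of at least one false positive.** The article gives no significance level and no family-wise figure, so there is nothing to reproduce. I assume one-sided 0.05 for each test, although sidedness is not stated for the visit-2 tests.
- Four independent tests: 1 − (1 − 0.05)^4 = 1 − 0.8145 = 0.1855.
- Correlated tests, simulated with no VR effect: 20 per sequence, normal data, t tests, 10,000 replicates per scenario. Assumed mYPAS correlation was 0.3 to 0.9 within a visit and 0 to 0.5 between visits. Result: 0.152 to 0.178, that is 3.0 to 3.6 times 0.05.
- All four two-sided, counting either direction: 0.151 to 0.179.
- At 0.025, independent: 1 − 0.975^4 = 0.0963.

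In the simulation the visit-1 and visit-2 test statistics were practically uncorrelated, which is why correlation within a visit lowers the rate only modestly. With one designated contrast the rate is 0.05.

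**The case against.** The strongest reply is that this is a pilot. Its declared focus is estimation, its scale-up rule (Feasibility Outcomes) uses serious adverse events, VR-related loss to follow-up and satisfaction, and no p-value triggers anything. No significance level is stated, and a multiplicity procedure is commonly left to an analysis plan, which is not shown. All of this stands. A reader might infer that the trial has an efficacy error rate three to four times nominal, or that the absence of an adjustment rule is itself the fault. The documents do not support either reading: the 0.15 to 0.18 applies only if any one of the four results is treated as success, and nothing in the article says it will be.

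A reader might also add the pain test and quote a single rate for five tests (0.19 to 0.21 in the same one-sided simulation). Pain and anxiety are separate aims, and the article does not treat them as one family.

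Nor do the visit-1 and visit-2 contrasts get pushed in opposite directions by a stable sequence difference, as one might suppose from the swap of groups. The difference cancels from the visit-1 change scores and shifts only the visit-2 raw scores.

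Finally, the T1 and visit-2 T0 comparisons may be meant to study anticipation or after-effects of earlier VR use. That is a reasonable question, and at visit 2 the VR-first sequence has indeed used VR before. The article does not say so, however, and lists these comparisons alongside the visit-1 ones without distinction. VR start times are recorded separately from laser times, so some play before T1 cannot be excluded; nothing in the article states it.

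These replies do not remove the inconsistency. The article itself fixes the time points, scales, tests and effect sizes, and they differ from its abstract and its outcome definition.

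**Conclusion.** The point holds as a problem of definition. Data Analysis specifies four mYPAS contrasts on two scales for an outcome listed as primary, designates none, and departs from the abstract and Primary Outcomes. On the stated timing, only one of the four contains a rating made after VR use at that visit. That conclusion depends on reading T0, T1 and T2 in the listed order and on VR being used during the procedure; it needs no significance level.

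The false-positive figure of about 0.15 to 0.18 is conditional on an assumed one-sided 0.05, assumed correlations, t tests standing in for the rank sum option, and a reader who counts any significant result. It shows what selective reading could cost and is not an error rate that the trial claims to control. The matter should be corrected, because the estimation purpose itself needs one designated anxiety effect size.

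**What to change.** Before the anxiety data are analysed by group, amend Data Analysis as follows:
- Name the T0-to-T2 change in mYPAS, VR versus control, as the single main anxiety contrast.
- Estimate it within participant across both visits, as Primary Outcomes describes, or state explicitly that it uses visit 1 only.
- Report the visit-1 T0-to-T1 change and the visit-2 T0 and T1 scores as descriptive, with estimates and 95% CIs.
- Carry only the main contrast's effect size into planning the next trial.

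The within-participant form also gains precision. If change scores have SD s and correlation r between visits, its variance is 2s²(1 − r)/40, against 2s²/20 for visit 1 alone, a ratio of (1 − r)/2. For an assumed r of 0 to 0.5 that is 0.50 to 0.25. The visit-1 form is less exposed to carryover, so the choice should be stated.

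The cost is wording only, since all six ratings are already planned. The downside is that a nominally significant result at another time point can no longer be presented as efficacy evidence. Data collection ended in November 2025 and analysis is in progress, so the change should be dated, and disclosed as late if group results have been seen. Ordering the anxiety contrast after pain, or a Holm adjustment across the two, is optional in a pilot.
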